**Methods:**

The trial will use a randomized controlled design comprising 47 intervention participants and 47 control group participants. Participants will be adults (age≥18 years) attending outpatient rehabilitation with limitations in their forearm, wrist, or hand function due to distal radial or ulnar fractures, stroke, or osteoarthritis. This study’s primary outcome variables are related to patients’ range of motion and strength, specifically active and passive wrist flexion and extension range of motion; active and passive forearm pronation and supination range of motion; grip strength; and pinch strength. The secondary outcome variables are related to patients’ perceived wrist pain and disability in activities of daily living. The patients’ perceived wrist pain and disability in activities of daily living will be measured using the patient-rated wrist evaluation questionnaire. The control group will receive the standard of care at each of the 2 hospital facilities (Glenrose Rehabilitation and Royal Alexandra Hospitals). The intervention group will receive the same standard of care as the control group at each facility and will use the FEPSim device for therapeutic activities to increase strength, range of motion, resistance, and dexterity. All the participants will be assessed at baseline (week 0); weeks 2, 4, and 8; and postintervention (week 10).

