### Outcome Variables

#### Primary Objective and Secondary Objectives 1 to 4: Primary Outcome Variables

The retention rates and intervention compliance will be calculated for the primary objective. The retention rates will be calculated according to the participants’ discontinuation of the interventions and their absence at the posttest at week 10. Intervention compliance means all of the hand rehabilitation sessions are completed by each group [21]. This study’s primary outcome variables for secondary objectives 1 to 4 are related to range of motion and strength: (1) AROM and PROM of wrist flexion and extension and forearm pronation and supination, (2) grip strength, and (3) pinch strength.

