#### Primary Objective and Secondary Objectives 1 to 4: Secondary Outcome Variables

The secondary outcome variables are the patients’ perceived wrist pain and disability in activities of daily living.

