### Data Analyses

#### Primary Objective and Secondary Objectives 1 to 4

Data analyses will be conducted using the intention-to-treat principle. Complete case analysis will be the primary method for dealing with missing data equal to or more than 10%. This is the most common method for dealing with missing data and reducing the risk of bias [27]. For missing data of less than 10%, we will use a simple imputation method by replacing the missing data with the average participants in the same strata (ie, medical condition). The analyses will focus on descriptive statistics and CI estimation rather than formal hypothesis testing [28]. Descriptive statistics will be used to characterize the groups at the pretest and posttest as well as during weeks 2, 4, and 8. The outcome variables as well as other data such as the length and dosage of each intervention will be summarized as n (%), mean (SD), or median (IQR), as appropriate. The retention rates, intervention compliance, and missing data will be summarized for outcomes related to the secondary objectives, which, together with the estimates, will assist in calculating the sample size for a definitive trial. As this study aims to assess the feasibility of conducting a definitive trial, clinical effectiveness is a secondary objective (ie, the study’s proof-of-concept element). In this regard, comparisons of the outcome variables at the pretest (week 0) and posttest (week 10) within the groups will be performed using a paired two-tailed *t* test (or a Wilcoxon signed-rank test if the data are not normally distributed) for AROM, PROM, grip strength, and pinch grip force and a Wilcoxon signed-rank test for the PRWE. Comparisons between the groups at the pretest and posttest will be performed using a *t* test (or a Mann-Whitney *U* test if the data are not normally distributed) for AROM, PROM, and grip strength and a Mann-Whitney *U* test for the PRWE. With our sample size, there would be a power of 0.8 to detect a medium effect size of Cohen *d*=0.25. However, we are aware that our study might be underpowered due to the sample size. If no statistically significant differences are found, our results will be classified as inconclusive rather than negative. We will report 95% CIs and interpret the level of uncertainty based on them [28]. In addition, we will explore the effects of the covariates using general linear models or multilevel mixed models when appropriate. All the α levels of significance will be set at *P*≤.05 (two-tailed).

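### The plan chooses confidence-interval estimation over testing, then tests every clinical measure at P≤.05 with no key measure and no caution about isolated significant results

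*Protocol article*

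**What the plan says.** All references are to the protocol article.

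- **Principle.** Data Analyses, for the primary objective and secondary objectives 1 to 4: "The analyses will focus on descriptive statistics and CI estimation rather than formal hypothesis testing".
- **Tests.** The same paragraph calls for paired t or Wilcoxon tests from week 0 to week 10 within each group. It also calls for t or Mann-Whitney tests between groups at week 0 and at week 10.
- **Threshold.** It closes with "All the α levels of significance will be set at" P≤.05, two-tailed.
- **Reading rule.** "If no statistically significant differences are found, our results will be classified as inconclusive rather than negative". It adds that 95% CIs will be reported and used to judge uncertainty. No sentence says how a significant result is to be read.
- **Measures.** Outcome Variables assigns retention and compliance to the primary objective and says that the "primary outcome variables for secondary objectives 1 to 4 are related to range of motion and strength": "AROM and PROM of wrist flexion and extension and forearm pronation and supination, (2) grip strength, and (3) pinch strength". These are not ranked among themselves. PRWE is placed below them: "The secondary outcome variables are the patients’ perceived wrist pain and disability in activities of daily living".
- **Labels elsewhere.** The Methods part of the Abstract says without qualification that the study's "primary outcome variables are related to patients", meaning their range of motion and strength. Table 1 lists the same measures under the heading of primary outcome.

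**The concern.** The paragraph gives two instructions that do not fit together. Under the first, the product is a set of estimates with intervals, and no result is sorted by a threshold. Under the second, every measure is declared significant or not at .05. A later analysis plan or report could follow either and claim to follow the protocol.

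The second instruction carries the risk. Several clinical measures share one label, none is singled out, and each is judged at an unadjusted .05. Non-significance is handled with care, but an isolated significant measure comes with no warning. The Abstract and Table 1 then supply a label that the objectives do not support. One chance result could therefore be presented as a significant effect on the primary outcome, when the primary objective is feasibility and effectiveness is a secondary, proof-of-concept question.

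**Working it through.** The plan states no number of tests and no overall error rate, so it has no figure of its own to reproduce here. The power statement under Sample Size is a separate matter and does not enter.

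**1. Count the measures** (Outcome Variables). Four directions (flexion, extension, pronation, supination) × 2 (active, passive) = 8 motion measures. Adding grip and pinch gives 10 primary clinical measures. Adding PRWE, taken as one total score, gives 11.

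**2. Count the tests as listed** (Data Analyses).
- Within groups: 11 measures × 2 groups = 22.
- Between groups: AROM, PROM, grip and PRWE are listed and pinch is not, so 8 + 1 + 1 = 10 measures. At 2 time points this gives 20: 10 at baseline and 10 at week 10.
- Total: 22 + 20 = 42, before any covariate model.

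**3. Decide which tests estimate the device effect.** Only the 10 between-group contrasts at week 10 do.
- The 10 baseline comparisons concern groups that have just been randomised.
- The 22 within-group tests measure change over ten weeks of therapy, which is expected in both arms. Simulating 47 per arm, with an assumed improvement of 0.5 SD in both arms and an assumed pre-post correlation of 0.5, about 92% of them were significant with no device effect at all.

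**4. Chance of at least one P≤.05 among the week-10 contrasts with no true effect.** If the k tests are independent, this is 1 − 0.95^k.
- k = 10: 1 − 0.95^10 = 1 − 0.599 = 0.401.
- k = 9 (the primary measures on the list, without PRWE): 1 − 0.95^9 = 1 − 0.630 = 0.370.

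**5. Allow for correlation.** The documents give no correlations, so a range is assumed. Test statistics were simulated as Z = √ρ·W + √(1−ρ)·E, with W shared across measures and E specific to each (200,000 draws), counting draws with any |Z| > 1.96.

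| Assumed ρ | k = 10 |
|---|---|
| 0 | 40% |
| 0.3 | 35% |
| 0.5 | 29% |
| 0.7 | 21% |

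Simulating actual t tests with 47 per arm (2,000 trials each) gave 41%, 36%, 29% and 22%, which agrees.

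**6. Sensitivity to the count.**
- If AROM and PROM are each treated as one variable, the week-10 contrasts number 4 (AROM, PROM, grip, PRWE). The chance is then 19% if independent and 13% at ρ = 0.7.
- Data Collection Methods also measures radial and ulnar deviation, which Outcome Variables does not name. Including them gives 12 + 1 + 1 = 14 contrasts: 51% if independent, and 44%, 35% and 25% at ρ = 0.3, 0.5 and 0.7.

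**The case against.** The best defence is that this is a feasibility study and the text already restrains itself. It sets out to explore effectiveness, calls it secondary, admits that the study may be underpowered, and commits to 95% CIs. A focus on estimation need not exclude supporting tests. Multiplicity procedures are commonly left to an analysis plan, which is not shown. The labels in the Abstract and Table 1 may be no more than shorthand for the fuller wording in Outcome Variables.

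Much of this stands. The absence of an adjustment procedure is not the point, and exploratory analyses need none when no threshold sorts the results. Here a blanket threshold is stated, in the paragraph that disclaims formal testing, and the CI commitment does not remove it.

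Three stronger readings are tempting, and the documents do not support them.

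- A reader might take all 42 tests and conclude that a chance finding is likely: 1 − 0.95^42 = 88% if independent. But 22 of those tests are within-group and 10 are at baseline. Neither kind estimates the device effect, so neither belongs in this risk.
- A reader might infer from the rule on non-significance that nothing can count against the device. The tests are two-tailed, so a significant difference in favour of control is possible, and the intervals are to be interpreted either way.
- A reader might call the clinical measures wholly unranked. PRWE is explicitly secondary; the lack of ranking is among the motion and strength measures.

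Nor is the sentence on non-significant results a defect. It is a sound safeguard in a small trial. What is missing is its counterpart.

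**Conclusion.** The point holds in this limited form. The analysis paragraph contradicts its own estimation principle by setting P≤.05 for every clinical test, names no key clinical measure, and cautions in one direction only. With no true device effect, the ten week-10 between-group contrasts give a chance of about 21% to 40% of at least one nominally significant result, which is four to eight times .05 but below even odds. For the nine primary measures among them it is 37% if independent.

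These figures assume that each motion direction is analysed separately, that PRWE is one score, and that correlations between measures are equal and lie between 0 and 0.7. A coarser or finer split moves the range as shown. The text does not say that one significant measure would establish effectiveness. It leaves that reading open, and the labels in the Abstract and Table 1 invite it. The wording should be corrected before outcome data are compared by group.

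**What to change.** In Data Analyses, for secondary objectives 1 to 4:

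- Remove the P≤.05 threshold. Report each week-10 between-group difference with its 95% CI, labelled exploratory and unadjusted.
- Keep the sentence on non-significant results. Add a matching one: no single nominally significant measure, and no within-group change, will be read as evidence of effectiveness.
- If a test is to be kept, name one week-10 between-group measure as the only tested outcome.

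In the Abstract and Table 1, label retention and compliance as the outcomes for the primary objective, and motion and strength as clinical outcomes for secondary objectives 1 to 4, in line with Outcome Variables.

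The cost is wording only; no data collection or sample size changes. The one downside is that a single nominally significant measure can no longer be headlined.

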#### Control Group

This group will receive the standard of care at each hospital, which consists of immobilization for 7 to 8 weeks (for fractures) after the time of the injury or surgery, followed by hand therapy sessions for 10 weeks to manage scar tissue, sensory modifications, and edema as well as therapeutic activities to increase strength, range of motion, and dexterity. These therapeutic activities will be carried out using the equipment and materials available at each hospital, including weights and elastic or gripping equipment and materials. The sessions’ length and frequency will depend on the patients’ needs and diagnoses. The length of each session will be between 30 minutes and 45 minutes, and they will be carried out once or twice per week.

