#### Primary Objective and Secondary Objectives 1 to 4: Confounding Variables

The confounding effects of the participants’ age, gender, and medical condition (distal radial or ulnar fractures, stroke, or osteoarthritis); whether the participants are taking any pain medication; what activities the participants perform at home or work; and the therapist providing the intervention will be determined.

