**Covariates**													
	Demographic variables	Patients		Self-report assessment questionnaire		✓							
	Medical condition (distal radial or ulnar fractures, stroke, or osteoarthritis)	Patients		Therapist records		✓							
	Whether the participant is taking any pain medication	Patients		Self-report assessment questionnaire		✓		✓		✓		✓	
	Activities the participant preforms at home or work	Patients		Self-report assessment questionnaire		✓		✓		✓		✓	

^a^T_0_: data collection point 1.

^b^T_1_: data collection point 2.

^c^T_2_: data collection point 3.

^d^T_3_: data collection point 4.

^e^AROM: active range of motion.

^f^PROM: passive range of motion.

^g^PRWE: patient-rated wrist evaluation.

^h^N/A: not applicable.

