### Allocation: Sequence Generation

Probability sampling stratified by medical condition (wrist fractures, acquired brain injuries, burns, or osteoarthritis) will be used. Random sequence generation will be prepared in advance by a research team member ([name]) on an Excel file spreadsheet (RAND function) using permuted block randomization with a block size of 4 and a ratio of 1:1.

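### The between-arm clinical comparison at week 10 uses neither the baseline value of the outcome nor the stratification factor, and the tests placed beside it do not estimate the FEPSim effect

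*Protocol article*

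**What the plan says.** The Data Analyses section (primary objective and secondary objectives 1 to 4) sets out three layers of analysis for the clinical outcomes.

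- **Within arms.** Week 0 is set against week 10 in each arm: these comparisons "within the groups will be performed using a paired two-tailed *t* test". The rank-based alternative is the Wilcoxon test.
- **Between arms.** "Comparisons between the groups at the pretest and posttest will be performed using a *t* test", or a Mann-Whitney test. The two time points are compared separately, and neither comparison has a baseline or stratum term.
- **Covariates.** As an addition, "we will explore the effects of the covariates using general linear models or multilevel mixed models when appropriate".

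Table 1 shows AROM, PROM, grip strength, pinch grip and the PRWE measured at the first data collection point. The section on allocation sequence says "Probability sampling stratified by medical condition (wrist fractures, acquired brain injuries, burns, or osteoarthritis) will be used", with permuted blocks of 4.

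The confounder list names age, gender, medical condition, "whether the participants are taking any pain medication; what activities the participants perform at home or work", and the treating therapist. Table 1 lists pain medication and activities as covariates and ticks both at all four data collection points. The baseline value of the outcome is in neither list.

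The same section says that the analysis focuses on description and confidence intervals, that clinical effectiveness is a secondary, proof-of-concept objective, and that non-significant results will be called inconclusive.

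**The concern.** The protocol collects two strong candidates for explaining outcome variance, the baseline value and the diagnosis, and then leaves both out of the comparison that estimates the effect of FEPSim. Differences between fracture, stroke and osteoarthritis patients, and between patients who start with good and poor function, go into the error term.

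This matters because the effect estimates, variances and 95% CIs are what the trial is meant to deliver for sizing a definitive trial (secondary objectives 3 and 4). Unadjusted intervals are wider than these data require. If the definitive trial adjusts for baseline, as is usual, the raw SD alone will not give its planners what they need.

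The accompanying tests add little. Randomisation makes the null hypothesis of a baseline test true by design. Both arms receive ten weeks of therapy, so improvement is expected in both, and a paired test within one arm cannot separate the device from recovery and standard care.

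**Working it through.** **Inputs from the protocol article.** 47 per arm and 30% dropout (Sample Size), so 47 × 0.7 = 32.9, about 33 completers per arm. Two-sided α of .05. Blocks of 4 within medical condition (Allocation).

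**Assumed inputs, not in the documents.** Correlation r between baseline and week 10: 0.3, 0.5 or 0.8. Share of outcome variance explained by medical condition: 0, 20% or 40%. Power of each within-arm test: 50%, 80% or 90%.

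**1. The plan's own figure.** The Sample Size section claims 80% power at d = 0.25. It does not reproduce: by the noncentral t distribution, a two-sample t test at d = 0.25 has power of 22% with 47 per arm and 17% with 33. That is a separate problem and this point does not rest on it. Baseline adjustment would not repair it: with 47 per arm and r = 0.8, power at d = 0.25 is still only about 52%.

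**2. Gain from baseline adjustment.** The unadjusted t test with 33 per arm has a detectable d at 80% power of 0.70. ANCOVA multiplies the variance by 1 − r², so the detectable d becomes 0.70 × √(1 − r²). The unadjusted number with the same precision is 33/(1 − r²).

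| r | 1 − r² | Variance cut | Detectable d | Equivalent completers per arm | Gain per arm |
|---|---|---|---|---|---|
| 0.3 | 0.91 | 9% | 0.67 | 36 | 3 |
| 0.5 | 0.75 | 25% | 0.61 | 44 | 11 |
| 0.8 | 0.36 | 64% | 0.42 | 92 | 59 |

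**3. Effect of leaving out the strata.** Trials of 92 patients were simulated, with blocks of 4 in three strata and r = 0.5 within strata.

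| Variance explained by condition | Type I error, unadjusted t test | Power at d = 0.5, unadjusted | With strata | With strata and baseline |
|---|---|---|---|---|
| 0 | 5.2% | 66% | 66% | 77% |
| 20% | 3.1% | 67% | 75% | 86% |
| 40% | 1.3% | 69% | 86% | 94% |

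Both adjusted models kept type I error near 5%. Stratified blocks balance condition between the arms, but the t test still counts condition as noise. Its standard error is therefore too large and its intervals over-cover.

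**4. Within-arm tests.** Suppose both arms truly improve equally and each paired test has power p. Exactly one arm is significant with probability 2p(1 − p):

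- p = 0.5: 2 × 0.5 × 0.5 = 50%
- p = 0.8: 2 × 0.8 × 0.2 = 32%
- p = 0.9: 2 × 0.9 × 0.1 = 18%

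These count both directions. The misleading pattern of FEPSim significant and control not is half of each: 16% at p = 0.8. The risk shrinks when recovery is large. For 33 pairs and an assumed standardised change of 0.8, the noncentrality is 0.8 × √33 = 4.6, power is about 99%, and discordance is about 1%.

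**The case against.** The strongest reply has four parts.

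- **The comparison is valid.** In a randomised trial the unadjusted week-10 difference is unbiased, and under stratified blocks its test is conservative. This stands: the loss is precision and interval width, not validity.
- **Effectiveness is secondary.** The plan stresses estimation and treats null results as inconclusive. This limits the severity. It does not remove the point, since interval width and variance are what an estimation-focused feasibility trial passes on.
- **Adjustment is already foreseen.** Medical condition and treating therapist are on the covariate list, and general linear and mixed models are named. This is partly right: the strata are not ignored in every model. But those models are an added exploration of covariate effects, and the baseline outcome appears in none of the lists.
- **Within-arm change has a purpose.** Secondary objective 2 concerns measuring change, and the Discussion wants the expected course over ten weeks. This stands for describing change with intervals. It does not require significance tests, although no section proposes to claim a FEPSim effect from them.

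A reader might also infer three stronger things that the text does not support.

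- *Planned adjustment for variables affected by treatment.* Table 1 records pain medication and activities after randomisation, but also at week 0, and no section says that later values will enter a model of the arm effect. What can be said is that the article sets no restriction.
- *Different equipment at the two hospitals.* The Control Group section says only that therapy is carried out "using the equipment and materials available at each hospital".
- *The wrong SD carried into the definitive trial.* The article does not say which SD will be used. The raw SD is right for planning an unadjusted comparison and conservative for an adjusted one.

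**Conclusion.** The concern holds as a matter of efficiency and reporting, not of bias. The stated between-arm comparison discards the baseline value of every outcome and leaves the stratification factor to exploratory models.

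The size of the loss depends on quantities that the documents do not give. It is small at a baseline correlation of 0.3 (a gain of about 3 completers per arm) and large at 0.8 (about 59). The over-wide intervals arise only to the extent that medical condition predicts outcome. The 32% discordance between within-arm tests rests on an assumed 80% power per arm.

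The change should be made, because it improves the estimates that the trial exists to provide. It is not an obstacle to running the trial.

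**What to change.** 1. State the main clinical estimate for each outcome as the week-10 difference between arms, adjusted for the week-0 value of that outcome and for medical condition, with its 95% CI, from the general linear or mixed model already named. The levels of medical condition should be those actually used in randomisation. The allocation section lists four conditions, including burns, while the eligibility criteria and Table 1 list three, so these need to be reconciled first.
2. Describe baseline characteristics by arm, and within-arm change with 95% CIs, without significance tests.
3. If pain medication and activities are used as covariates in a model of the arm effect, restrict them to week-0 values. Later values may be affected by treatment and can be reported descriptively.
4. Report the residual SD, or the baseline to week-10 correlation, beside the raw SD, so that the definitive trial can be planned for either analysis.

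All the variables are already collected. The cost is a change of wording and a few degrees of freedom.
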